## Introduction

### Overview

Orthodontic treatment is a common health care intervention; the most recent National Child Dental Health Survey (England, Wales, and Northern Ireland) indicated that 9% of 12-year-old children are receiving orthodontic treatment, and a further 37% have an unmet need [1]. Treatment duration can be lengthy (2-3 years on average), and adherence to treatment advice is therefore essential for successful outcomes [2]. Failure to adhere to treatment advice can mean that treatment objectives are not met, and there may be detrimental effects on dental health. For example, failing to adhere to dietary advice may result in breakage of the braces and increased overall treatment time, and nonadherence to dietary and oral hygiene advice during treatment can lead to avoidable tooth decay and gum disease.

The National Health Service (NHS) experiences significant costs as a result of nonadherence to treatment [3], and orthodontics is no exception to this. One multicenter study found that 43% of patients failed to complete treatment, and there were no useful predictors for this [4]. To put this into perspective, the NHS England annual expenditure on primary-care orthodontic treatment alone is in excess of £200 million (US $267 million) [5]; noncompletion of treatment therefore represents a significant inefficient use of public resources.

Improving adherence is complex and necessitates a change or modification of existing behavior. A contemporary and widely accepted framework based on multiple models of behavior change developed by Michie et al [6] is the behavior change wheel (BCW). The COM-B model forms the core of the BCW and proposes that individuals need capability (C), opportunity (O), and motivation (M) to perform or adapt a particular behavior (B).

Attempts to improve adherence to treatment advice in orthodontics have included utilizing mind maps and multimedia-assisted methods of providing information. Although these methods have been shown to significantly increase knowledge [7-9], this does not necessarily equate to better adherence to treatment advice or better outcomes [8]. A recent systematic review considered techniques including the use of motivational tests, the Hawthorne effect, and the use of awards and rewards, concluding that there is insufficient evidence to recommend a single method to improve patient adherence to treatment and that more research is required in this area [10].

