### Aims

This study will assess the quality, effectiveness, and acceptability of the My Braces app and test the following primary hypothesis:

Using the full functionality of the My Braces app improves adherence to oral hygiene advice in patients undertaking fixed brace treatment.

The secondary hypothesis is as follows:

Using the full functionality of the My Braces app improves adherence to orthodontic treatment advice (reduction in fixed appliance breakages, missed and rescheduled appointments, treatment duration, number of appointments, and enamel demineralization).

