#### Data Collection

A complete data set will be collected at baseline, 3 months into treatment, 12 months into treatment, and at the end of treatment when the orthodontic appliances have been removed.

Two primary outcome measures have been selected, a health behavior outcome and a clinical outcome, as both are felt to be important. The outcome measures are timed toothbrush use and gingival bleeding scores (these scores indicate the amount of bleeding from the gums, where bleeding is an indicator of inadequate toothbrushing).

The secondary outcomes of interest are as follows: plaque scores, which indicate the amount of plaque on the teeth, where retention of plaque is an indicator of inadequate toothbrushing; number of fixed appliance breakages; number of missed and rescheduled appointments; treatment duration, number of appointments (including emergency appointments for appliance breakages); enamel demineralization (early tooth decay) on the upper anterior six teeth (using standardized photographs), as demineralization is a further indicator of inadequate toothbrushing and nonadherence to the appropriate diet; subjective quality of the app (sections E and F of the uMARS questionnaire); and app engagement.

The following baseline measurements and details will be obtained prior to treatment commencing: age, gender, malocclusion (type of dental bite), whether or not extractions (removal of teeth) are required for treatment, clinical photographs of the teeth (these will be compared with completion of treatment photographs to assess for enamel demineralization), bleeding score, and plaque score.

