##### Other Outcomes

Information relating to treatment duration and the number of breakages (for example, detachment of the brace from the tooth, displacement of the brace wire), missed or rescheduled appointments, and emergency appointments will be obtained from the patient’s medical records. Data relating to the subjective quality score for the app will be obtained by way of patient-completed paper questionnaires (sections E and F of the uMARS form). Furthermore, app engagement will be determined via the data available on Google’s Firebase system.

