#### Planned Analyses

Proposed outcome analyses are summarized in Table 2.

For each of the main outcome measures, it is anticipated that regression analysis will be undertaken. The main factor of interest (group allocation) and confounding variables (eg, age, gender, ethnicity) will be entered into univariable regression analyses to determine the level of significance and to limit the number of variables entered into the multivariable analysis. Any factors with *P*≤.10 will be considered for inclusion in the multivariable analysis. Factors with *P*<.05 in the multivariable analysis will be considered as having a significant effect on toothbrushing time or gingival bleeding. Secondary outcomes will be explored in a similar manner.

If necessary, an intention to treat analysis will be performed; all enrolled and randomized patients will be included in the analysis and analyzed in the groups to which they were randomized.

**Table 2 table2:** A summary of proposed statistics for outcome analysis.

Outcomes	Method of analysis
Toothbrushing duration	Comparison of the 3 groups using an ANOVA, followed by 2-sample *t* tests (A vs B, B vs C, and A vs C) if any statistical significance is found
Bleeding score	Chi-square test
Plaque scores	Comparison of the 3 groups using an ANOVA, followed by 2-sample *t* tests (A vs B, B vs C, and A vs C) if any statistical significance is found
Number of breakages	Kruskal-Wallis test, followed by Mann-Whitney test (A vs B, B vs C, and A vs C) if any statistical significance is found
Number of missed appointments	Kruskal-Wallis test, followed by Mann-Whitney test (A vs B, B vs C, and A vs C) if any statistical significance is found
Total number of appointments	Kruskal-Wallis test, followed by Mann-Whitney test (A vs B, B vs C, and A vs C) if any statistical significance is found
Treatment duration	Comparison of the 3 groups using an ANOVA, followed by 2-sample *t* tests (A vs B, B vs C, and A vs C) if any statistical significance is found
Enamel demineralization	Chi-square test
App subjective quality	Comparison of the 3 groups and different section of the uMARS form by using the Kruskal-Wallis test.
App engagement	Comparison of the 3 groups using an ANOVA, followed by 2-sample *t* tests (A vs B, B vs C, and A vs C) if any statistical significance is found

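### A lower total number of appointments is counted as better adherence, but stopping treatment early also lowers it, so a fall cannot be interpreted

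*Protocol article*

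**What the plan says.** The secondary hypothesis (Aims) defines better adherence to treatment advice as a "reduction in fixed appliance breakages, missed and rescheduled appointments, treatment duration, number of appointments, and enamel demineralization". The direction of benefit for the number of appointments is therefore fixed: fewer is better.

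The Phase 2 Data Collection section lists the outcome as one count, the "number of appointments (including emergency appointments for appliance breakages"). It lists the "number of missed and rescheduled appointments" as a separate outcome. Follow-up closes "at the end of treatment when the orthodontic appliances have been removed", with no distinction between planned completion and early removal.

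Under Other Outcomes, "missed or rescheduled appointments, and emergency appointments will be obtained from the patient’s medical records"; breakages and treatment duration come from the same source. Table 2 (Planned Analyses) gives the test: "Total number of appointments Kruskal-Wallis test, followed by Mann-Whitney test". Emergency appointments have no row of their own, and treatment completion is neither a listed outcome nor a row.

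The Introduction gives the background: "One multicenter study found that 43% of patients failed to complete treatment". The Abstract's Conclusions and the Discussion both propose that mobile phones will help more patients complete treatment.

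**The concern.** A patient who stops treatment early has no further visits. Other things equal, that patient's total is low, and the Aims score a low total as success. Non-completion is the problem that the protocol sets out to reduce, yet on this outcome it counts as a gain.

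The reverse also applies. If the full app keeps more patients in treatment, Group C accumulates more visits and can appear to do worse. Nothing else in the outcome list would expose the misreading, because completion is not reported as an outcome. A significant difference in this row, in either direction, would then be uninterpretable as evidence for the secondary hypothesis.

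**Working it through.** The plan gives no figure to reproduce here. The sample size rests on the two primary outcomes, and the number of appointments has no power calculation. The check is therefore on the direction of each effect, followed by an illustration of size.

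**Direction.** Write the expected number of visits per patient as

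[V(1 − m) + V·m·r + V·b] × [(1 − q) + q·f]

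where V = planned routine visits, m = share missed, r = replacement visits per missed visit, b = emergency visits per routine visit, q = share stopping early, and f = fraction of treatment reached by those who stop. None of these values is in the article for this outcome. V = 20 and b = 0.10 are assumed below.

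*Emergency visits.* The total rises with b in every case.

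*Early stopping.* The total falls by the proportion q(1 − f), whatever V, m, r and b are, and whether booked or attended visits are counted. With no missed visits, full completion gives 20 + 20 × 0.10 = 22 visits.

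| q | f = 0.75 | f = 0.50 | f = 0.25 |
|---|---|---|---|
| 10% | 21.45 (−2.5%) | 20.90 (−5.0%) | 20.35 (−7.5%) |
| 20% | 20.90 (−5.0%) | 19.80 (−10.0%) | 18.70 (−15.0%) |
| 43% | 19.64 (−10.7%) | 17.27 (−21.5%) | 14.91 (−32.2%) |

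*Missed visits.* The sign depends on a counting rule that the article does not state. With attended visits counted and all patients completing:

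| Replacement r | 5% missed | 20% missed |
|---|---|---|
| 0 (none replaced) | 19 + 0 + 2 = 21.0 | 16 + 0 + 2 = 18.0 |
| 0.5 | 19 + 0.5 + 2 = 21.5 | 16 + 2 + 2 = 20.0 |
| 1 (all replaced) | 19 + 1 + 2 = 22.0 | 16 + 4 + 2 = 22.0 |
| 1.25 (treatment prolonged) | 19 + 1.25 + 2 = 22.25 | 16 + 5 + 2 = 23.0 |

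More missed visits lower the total, leave it unchanged or raise it, depending on r.

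**Size of a retention effect.** Assume 30 months planned, within the 2 to 3 years given in the Introduction, and stops averaging 15 months. Mean time in treatment is (1 − q) × 30 + q × 15.

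- Early stopping falls from 20% to 10%: 0.80 × 30 + 0.20 × 15 = 27.0 months, against 0.90 × 30 + 0.10 × 15 = 28.5 months. The ratio is 28.5/27.0 = 1.056, about 6% more.
- Early stopping falls from 43% to 25%: 0.57 × 30 + 0.43 × 15 = 23.55 months, against 0.75 × 30 + 0.25 × 15 = 26.25 months. The ratio is 26.25/23.55 = 1.115, about 11% more.

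The 43% is the protocol's background figure, and the 20% borrows its planning dropout. The 25%, the 10% and the 15 months are assumptions. At a constant visit rate, the number of visits rises in the same proportion.

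**Analysis.** Kruskal-Wallis and Mann-Whitney tests rank the totals, so early stoppers tend to fall at the low end, which the Aims treat as the good end. Planned Analyses also foresees regression for secondary outcomes, but the covariates it gives as examples are age, gender and ethnicity. Time in treatment is not among them.

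**The case against.** The strongest defense is that the protocol has a sound reason for its direction. The Introduction says that ignoring dietary advice can break the brace and lengthen treatment. Breakages add emergency visits, and longer treatment adds routine ones. Among patients who finish, fewer appointments can therefore reflect better adherence. This stands, and it is why the outcome is best described as mixed rather than simply reversed.

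A reader might infer two stronger points. The first is that every missed routine visit lowers the total, so this outcome works against the missed-appointments outcome. The article does not say that attended rather than booked visits are counted, nor that missed visits go unreplaced. If they are rebooked or prolong treatment, the two outcomes do not conflict. The second is that the outcome rewards non-adherent patients in general. It does not, because breakages and prolonged treatment count against them.

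It is also fair to say that breakages and missed appointments each have their own Table 2 row, that this is one unpowered secondary outcome, and that the trial's planning dropout is 20%, well below 43% (although trial dropout and stopping treatment are not the same thing). These points limit the weight of the finding. They do not remove the early-stopping problem: its direction holds under any counting rule, and the direction of benefit is already fixed in the Aims.

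The full protocol or an analysis plan may define the count more closely. A definition of booked or attended visits would settle the missed-visit question, but not the effect of early stopping.

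**Conclusion.** The point holds for early stopping. As the plan is written, a reduction in total appointments can come from fewer breakages and shorter completed treatment, or from more patients leaving treatment, and the planned comparison does not separate these. Better retention could be read as a worse result.

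The direction follows from the text. The size does not: the increases of about 6% and about 11% rest on 30 planned months, stops averaging 15 months, a constant visit rate and the assumed changes in early stopping. Missed visits are only a conditional second route.

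Treatment duration has the same weakness, since a treatment abandoned early is also a short one and the Aims count shorter as better. The primary outcomes and the sample size are unaffected. This is an inexpensive improvement to a secondary outcome that should be made before recruitment starts.

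**What to change.** In Aims, Phase 2 Data Collection and Table 2:

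- Replace total number of appointments, as the tested adherence outcome, with emergency (unscheduled) appointments per month in treatment. Both components, emergency appointments and treatment duration, are already to be taken from medical records under Other Outcomes.
- Keep total appointments as a descriptive resource-use figure, shown by completion status, next to the number completing treatment in each group.
- Do not present a completers-only comparison as a randomized one. Completion occurs after randomization and may itself be changed by the app.
- Show treatment duration by completion status as well, since it shares the weakness.

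The cost is outcome wording and one Table 2 row, with no extra visits or measurements. Completion status is not named among the items extracted and would have to be noted from the same records. The article reports that no patients had been recruited, so the change comes before any data. The downsides are that one listed secondary outcome becomes descriptive and that the replacement partly overlaps with the breakages outcome. A monthly rate also removes only the mechanical effect of time in treatment; it does not correct for emergency visits that cluster in one part of treatment.

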#### Methods of Outcome Assessment

##### Timed Toothbrush Use

Timed toothbrush use will be determined via the information stored on the app. It is anticipated that participants will not remember to time every brushing episode; therefore, the duration and number of brushing sessions stored within the app will allow for the average brushing duration to be determined. The unit of measurement will be seconds.

##### Gingival (Gum) Bleeding

A periodontal probe (specialized probe to test gum health) will be used; the presence of bleeding within 10 to 30 seconds of probing is indicative of inflammation of the gingivae (gums). Scores will be recorded for all teeth anterior to the molars (incisors, canines, and premolars) and will be recorded as the percentage of the total number of tooth surfaces (6 surfaces per tooth). A binary score will be assigned to each surface (1 for bleeding present, 0 for no bleeding).

A calibration exercise will be conducted prior to commencing the study. The key factors affecting consistency of probing technique are probe position and pressure applied (ideally 20 to 25 grams). The bleeding assessment technique will therefore be reviewed and observed in a volunteer subject by a gold standard examiner following training performed on models. It is not possible to do duplicate bleeding assessments as the act of repeated probing can cause bleeding; therefore, it is essential that this aspect of the study is well controlled for.

##### Plaque Scores

Plaque scores will be recorded for all teeth anterior to the molars (incisors, canines, and premolars) as the percentage of total surfaces (6 surfaces per tooth). A plaque disclosing agent (a temporary dye that is retained on the plaque to make it visible) will be used for the plaque assessment. A binary score will be assigned to each surface (1 for plaque present, 0 for no plaque present) [18].

Prior to the initiation of the study, 10 non–study subjects with similar characteristics to those who will be included in the study will be recruited for an examiner calibration exercise. A request for volunteers will be made from current patients within the orthodontic department. The designated examiner ([name]) will measure full mouth plaque scores in the manner described for all 10. This will be repeated on the same day (at least 15 minutes apart to reduce memory bias); the examiner will evaluate the same subjects for a second time with no brushing undertaken in between. Subjects will be redisclosed for the second plaque scoring.

Intra-examiner repeatability for plaque measurement will then be assessed.

##### Enamel Demineralization

Before placing the orthodontic braces, teeth will be polished with a rubber cup and fluoride-free pumice paste and dried with air, and standardized digital photos will be taken under identical lighting conditions and with the same camera settings. These will be used to assess for enamel demineralization [19]. Three photographs will be obtained (front, right, and left with the teeth biting together) and stored securely.

At the end of treatment, the brace and the adhesive used to secure it to the teeth will be removed, and the teeth will be polished with a rubber cup and fluoride-free pumice paste and dried with air. A further series of standardized photographs will be obtained.

For the evaluation of demineralization, photographs will be assessed, and the severity of enamel demineralization will be recorded. The labial surfaces of the upper incisors and canines will be scored as follows [20]: (1) no white spot formation, (2) slight white spot formation (thin rim), (3) excessive white spot formation (thicker bands), or (4) white spot formation with cavitation.

A random sample of photographs will be re-examined after 1 month to check reliability.

These photographs are an essential part of routine orthodontic records for all patients, and therefore no additional patient appointments or increase in appointment time will be needed.

##### Other Outcomes

Information relating to treatment duration and the number of breakages (for example, detachment of the brace from the tooth, displacement of the brace wire), missed or rescheduled appointments, and emergency appointments will be obtained from the patient’s medical records. Data relating to the subjective quality score for the app will be obtained by way of patient-completed paper questionnaires (sections E and F of the uMARS form). Furthermore, app engagement will be determined via the data available on Google’s Firebase system.

#### Blinding

The outcome assessor will be blinded; however, given the nature of the intervention, it is not possible to blind the patient.

#### Sample Size

The following assumptions have been made in the sample size calculation:

Data are normally distributed and initial comparison of the 3 groups would use an analysis of variance (ANOVA), followed by 2-sample *t* tests for A versus B, B versus C, and A versus C if any statistical significance is found.

The significance level is *P*<.05 with 80% power.

##### Timed Toothbrush Use

Using a clinically relevant difference of 20 seconds between groups and a SD of 23.6 seconds from a paper by Tesini and Perlman [21] (standardized difference=0.85) and accounting for multiple testing, 29 patients are required in each group (n=87). Assuming a dropout of 20%, the sample size is 35 per group.

##### Gingival Bleeding

An estimated clinically relevant difference of 15% and a SD of 20% (standardized difference=0.75) was used, based on advice from [name] (clinical trials coordinator, Restorative Dental Sciences, UCL Eastman Dental Institute, Faculty of Medical Sciences, UCL), who has experience in commercial trials using these outcome measures. The same assumptions were followed as described above, and this indicated a sample size of 38 per group. With the 20% dropout factored in, the sample size calculation is 46 per group (n=138).

Therefore, 138 patients will be recruited. There are a number of assumptions in these calculations; therefore, an internal pilot will be conducted, and the calculations will be repeated using 3-month data for the first 15 patients recruited to each group.

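### The 20% dropout allowance is applied as n × 1.2 rather than n / 0.8, so 138 recruits leave about 37 per group, not the stated 38; the effect on power is small

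*Protocol article*

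**What the plan says.** The Sample Size section of the protocol article sets the general terms: "The significance level is *P*<.05 with 80% power". It plans an ANOVA across the three groups, "followed by 2-sample *t* tests for A versus B, B versus C, and A versus C if any statistical significance is found".

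For gingival bleeding, one of the two primary outcomes, it gives the inputs: "An estimated clinically relevant difference of 15% and a SD of 20% (standardized difference=0.75) was used". It continues: "The same assumptions were followed as described above, and this indicated a sample size of 38 per group". The inflated figure follows: "With the 20% dropout factored in, the sample size calculation is 46 per group (n=138"). This calculation fixes the target: "Therefore, 138 patients will be recruited".

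For brushing time, the other primary outcome, the section says that, "accounting for multiple testing, 29 patients are required in each group (n=87"), and then: "Assuming a dropout of 20%, the sample size is 35 per group".

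The Gingival Bleeding subsection adds that an internal pilot will redo the calculations on 3-month data from the first 15 patients in each group. It gives no inflation formula for that step.

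**The concern.** The 38, the 20% and the 46 stand together in one subsection and do not agree. Removing 20% of 46 does not leave 38. Both inflated figures equal the evaluable number times 1.2, rounded up. That is the usual slip of adding the dropout percentage to the evaluable number instead of removing it from the recruited number.

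The figure affected is the recruitment target itself. The plan in effect promises 38 evaluable patients per group after a 20% loss, and 138 recruits do not deliver that. The dropout margin may also be needed: data are collected to the end of treatment, which the Introduction puts at two to three years on average.

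**Working it through.** **Inputs from the Sample Size section:** overall significance level 0.05; power 80%; bleeding difference 15, SD 20, d = 0.75; 38 evaluable per group; 20% dropout; 46 per group, 138 in total. For brushing time: d = 0.85, 29 evaluable, 35 inflated.

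**Assumptions for the power figures only:** two-sided testing, and Bonferroni over the three pairwise comparisons (0.05/3 = 0.0167). The article says that it allows for multiple testing but names neither the method nor the sidedness.

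**1. Reproduce the evaluable number.** Normal approximation: n = 2(z₁₋α/₂ + z₁₋β)² / d² = 2 × (2.394 + 0.842)² / 0.75² = 37.22, rounded up to 38. This matches. An unadjusted 0.05 would give 28. The exact t test at 0.05/3 gives 38.7, that is 39, so the normal approximation is the plan's apparent method.

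**2. Reproduce the inflated numbers.**

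| Outcome | Evaluable | n × 1.2 | Stated | n / 0.8 |
|---|---|---|---|---|
| Bleeding | 38 | 45.6 → 46 | 46 | 47.5 → 48 |
| Brushing time | 29 | 34.8 → 35 | 35 | 36.25 → 37 |

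Both stated figures match n × 1.2 and neither matches n / 0.8.

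**3. What 138 leaves.**
- At 20% loss: 46 × 0.8 = 36.8 per group; 138 × 0.8 = 110.4 in total, against 3 × 38 = 114 required.
- Loss at which 38 remain: 1 − 38/46 = 17.4%.
- Number that keeps 38 at 20% loss: 48 per group, since 48 × 0.8 = 38.4. The total is 144, which is 6 more than 138 (6/138 = 4.3%).

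**4. Power for d = 0.75 at two-sided 0.05/3.**

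| Analysed per group | Normal approximation | t test |
|---|---|---|
| 38 | 80.9% | 79.1% |
| 37 | 79.7% | 77.9% |
| 36.8 | 79.5% | 77.6% |
| 36 | 78.5% | 76.5% |

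The slip costs about 1.4 to 1.5 percentage points on either method.

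**5. Brushing time.** With 36.8 analysed per group, this outcome exceeds its required 29.

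**The case against.** The best defence is that the shortfall hardly matters. The 38 is itself rounded up from 37.22 and carries 80.9% power on the plan's apparent method. On that method 46 per group keep 80% power up to 1 − 37.22/46 = 19.1% loss, so the 20% allowance is missed by about one percentage point. Power at 20% loss is 79.5%, which rounds to the stated 80%. If only 80% power had to be kept, 37.22/0.8 = 46.53, that is 47 per group (141), would do: 47 × 0.8 = 37.6, with 80.5% power. The SD rests on expert advice and is due to be checked in the internal pilot. An SD of 21 in place of 20 would raise n by (21/20)² − 1 = 10%, more than this slip does.

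All of that stands and limits the size of the point. It does not make 46 less 20% equal to 38. It also rules out several stronger readings that a reader might infer:

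- **That 80% power holds only up to 17% loss.** The 17.4% is the loss that leaves 38 patients. The 80% power limit is about 19.1%.
- **That the slip takes power from 80% to about 78%.** The 77.6% is a t-test figure. By the t test, 38 per group has only 79.1% before the slip counts, so part of that gap comes from the change of method.
- **That brushing time is also short.** Its inflated figure has the same slip, but the bleeding calculation sets the target, and 36.8 exceeds 29.
- **That the internal pilot will repeat the error.** The article says only that the calculations will be redone. Carrying the slip forward is possible but not documented.

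**Conclusion.** The point holds as a small sample-size correction. At the stated 20% dropout, the target of 138 leaves 36.8 per group and not the stated 38; 38 would need 144. This follows from the stated 38, 20% and 46 alone and does not depend on the multiplicity method or the sidedness. The power figures (79.5% instead of 80.9%, or 77.6% instead of 79.1% by the t test) rest on two-sided 0.05/3, which is assumed because it reproduces 38. The shortfall is about one analysed patient per group. It does not undermine the design, and the documents do not support calling the trial materially underpowered on this ground. It is worth correcting because the wrong figure is the recruitment target.

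**What to change.** Choose one of two restatements in the Gingival Bleeding subsection:

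- **Keep 138.** Say that 46 per group retains 38 evaluable patients up to about 17% loss and leaves about 37 per group at 20% loss, with about 79.5% power by the normal approximation at two-sided 0.05/3. If the t-test figure is preferred, name that method beside it.
- **Keep 38 evaluable at 20% loss.** State 48 per group, 144 in total.

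In either case, change 35 to 37 per group under Timed Toothbrush Use for consistency, with no effect on the target. State that the internal pilot recalculation will use n / (1 − 0.20), so that the slip is not carried forward.

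The first option costs a sentence or two and a slightly less favourable statement. The second costs six more patients. The article reports that no patients had yet been recruited, so on its account either change comes before enrolment.
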